### 2.3. Screening Process

The purpose of the staged screening process is to (1) verify eligibility; (2) obtain the participant’s informed consent; (3) complete baseline measurements; and (4) perform randomization.

The study will include several screening steps before randomization:A preliminary screen will be completed to determine eligibility either by phone or at the FMH-UL in separate visits to eliminate a substantial proportion of ineligible volunteers;Debriefing session for potential participants will be provided at FMH-UL with information about the study, including clarification of possible questions;Visit 1, taking place at FMH-UL, will consist of a physician appointment and a first informed consent form required for laboratory visit 1. It should be completed within 1 week after the debriefing session;Laboratory visit 1 will be required for participants to use accelerometers for PA assessment, individual calibration of motion sensors, and to fill dietary records (1 week). Successful completion will be required for eligibility. A second informed consent will be obtained for visits 2 and 3, which must be completed within 1 week;Laboratory visits 2 and 3 will include body composition, resting energy expenditure, physical fitness measurements, blood sample collection, eating-related measurements, and the completion of an exercise motivation questionnaire and a quality of life questionnaire. At the end, a third informed consent will be obtained to allow program enrollment.

Flexibility and alternative approaches in scheduling these steps are expected due to varying local circumstances, but all screening procedures will take place before randomization to guarantee each participant’s eligibility. Additional screening visits may be required due to time constraint issues.

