#### 3.3.6. Statistics

Statistical analysis will be performed using IBM SPSS statistics version 24.0 (IBM, Chicago, IL, USA). To test the normality of distribution of the variables, the Kolmogorov–Smirnov test will be performed. Descriptive statistics will be calculated (mean, standard deviation, and range). If normality is not achieved in some variables, non-parametric methods will be used. Repeated measures with Bonferroni corrections for adjusted comparisons will be used to determine any differences between conditions at the three moments and for changes between the intervention and control groups over time in primary and secondary outcomes. For exploring the association between changes in body composition and metabolic parameters, linear mixed regression models will be conducted. Statistical significance will be set at *p* < 0.05.

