#### 3.3.7. Sample Size

For sample and power calculations, this study is powered on changes in total body fat assessed by DXA. We consider a type I error of 5% and a power of 80% (using the software GPower version 3.1.9.2) to detect an effect size of 0.58 for statistically significant differences in total body fat as reported elsewhere [78]. A total of 37 participants per group will be required. Considering a 20% drop out rate, as occurred in the selected study [78], we will enroll 94 participants (47 in each group).

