In addition, prior research has shown an increase in upper and lower body strength after diet and exercise programs [84]. Other studies have shown that after lifestyle interventions, an increase of cardiorespiratory fitness occurs [84,85,86]. Therefore, it is expected that after the Champ4life intervention, participants reveal an increase in physical fitness, leading to higher muscle quality, better cardiorespiratory fitness, and lower mortality [86].

We also expect to understand the metabolic and behavioral compensations that may occur during weight loss and maintenance. We aim to find any compensations which lead to the retake of initial weight, like changes in energy intake and expenditure [20], spontaneous PA [21], and adaptive thermogenesis [22]. The current literature shows that when we increase EE (by increasing PA), we may compensate by increasing sedentary behavior, decreasing lifestyle PA and/or increasing energy consumption during the rest of the day [87]. The mechanisms underlying adaptive thermogenesis (i.e, mainly the decrease in REE and PAEE), beyond what can be predicted from the changes in FM and FFM in response to a restricted EI [19], are unclear when modest weight loss is expected. The mechanisms underlying the interplay between PA and alterations in eating behaviors and dietary intake (in terms of quantity and quality) also require further exploration, in order to improve interventions’ efficacy.

A significant strength of the Champ4life program will be the SDT-based intervention, providing tools for the adoption and sustainability of healthy behaviors through the development of autonomous motivation and self-regulatory skills [30,32,83]. Some limitations are anticipated in this study and should be addressed, in particular the effect of confounding variables such as the large age range (18–65 years) of participants eligible to be included, retirement years, and an unbalanced gender representation, provided there are more male former athletes than females.

To address these issues, the analysis will be controlled for the potential effects of these confounders. In addition, the prevalence of eating disorders is higher among athletes, especially in those engaged in weight-sensitive sports [88,89], and this may also be the case with former athletes; still, this aspect might not be appropriately captured by initial screening procedures (relying on yes/no answers) and thus will constitute a limitation of the present study.

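### The analysis sentence mixes between-arm tests of levels at all three moments, including pre-randomisation baseline, with a test of changes, names none as decisive, and omits the baseline value as a covariate

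*Protocol article*

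**What the plan says.** The comparative analysis in the Protocol article, section 3.3.6 (Statistics), is one sentence, and it applies to the primary and the secondary outcomes alike. It opens "Repeated measures with Bonferroni corrections for adjusted comparisons will be used". As to purpose, it says that this method "will be used to determine any differences between conditions at the three moments and for changes between the intervention and control groups over time". This covers two families of contrast: arm against arm at each of three moments, and arm against arm on change. The sentence does not say which is primary or how many comparisons the Bonferroni correction covers.

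The legend to Table 1 defines M1 as baseline. Section 2.3 (Screening Process) lists baseline measurement as a step before randomisation and adds that "all screening procedures will take place before randomization to guarantee each participant’s eligibility".

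The Introduction states the primary aim as a reduction in total and abdominal fat mass over 12 months. Section 3.3.7 (Sample Size) says "this study is powered on changes in total body fat assessed by DXA".

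The Discussion lists the wide age range, years since retirement and unbalanced gender as confounders, and says "the analysis will be controlled for the potential effects of these confounders". Baseline fat is not among them.

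**The concern.** Two parts of the planned sentence add little or do harm.

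- **The M1 comparison.** Both arms are then samples from one population, not yet randomised. A significant result can only be chance, and a non-significant one is uninformative. If Bonferroni runs over the three moments, this comparison takes a third of the alpha from the two that matter.
- **The level comparisons at 4 and 12 months.** Each carries the full between-person spread in fat mass and any chance difference between the arms at baseline. Every randomised participant has a baseline DXA value that would remove most of both, but it is not named as a covariate.

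Because no contrast is named as decisive, the level and change comparisons could give different answers for total fat from the same data, with no stated rule for which one counts.

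**Working it through.** **The plan's own figure.** For two means with standardised effect 0.58, 5% type I error and 80% power, n per arm = 2(z_α + z_β)²/0.58².

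- One-sided: 2(1.645 + 0.842)²/0.3364 = 36.8, so 37. The exact t calculation gives 37.5.
- Two-sided: 2(1.960 + 0.842)²/0.3364 = 46.7, so 47. The exact t calculation gives 47.6, so 48.
- Dropout: 37/(1 − 0.20) = 46.25, so 47 per arm and 94 in total, as stated.

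Among the two-sample formulas, 37 is reached only with a one-sided test. The article does not state sidedness. That is a separate matter. It explains why the change test below has 69% and not 80% power at two-sided 5%.

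**Inputs for the comparison**

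- 37 analysed per arm and effect size 0.58 (section 3.3.7).
- Assumption: two-sided 5%.
- Assumption: 0.58 is in units of the SD of change. The article says only "to detect an effect size of 0.58 for statistically significant differences in total body fat", without a standardiser.
- Assumption: correlation r between baseline and follow-up fat from 0.5 to 0.95. The article gives none.
- Assumption: equal variances at baseline and follow-up, and no other covariates.

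**Formulas.** With SD the spread of fat-mass levels:

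- SD of change = SD·√(2(1 − r))
- residual SD after adjustment for baseline = SD·√(1 − r²)

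Holding the treatment effect fixed:

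- d_change = 0.58
- d_level = 0.58·√(2(1 − r))
- d_adjusted = d_level/√(1 − r²)

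Example at r = 0.9: d_level = 0.58 × √0.2 = 0.259, and d_adjusted = 0.259/√0.19 = 0.595.

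**Power (noncentral t, 37 per arm, two-sided 5%)**

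| r | d_level | level test | change test | baseline-adjusted | adjusted minus level | adjusted minus change |
|---|---|---|---|---|---|---|
| 0.5 | 0.580 | 69% | 69% | 81% | 12 | 12 |
| 0.7 | 0.449 | 48% | 69% | 76% | 28 | 7 |
| 0.8 | 0.367 | 34% | 69% | 74% | 39 | 5 |
| 0.9 | 0.259 | 20% | 69% | 71% | 52 | 2 |
| 0.95 | 0.183 | 12% | 69% | 70% | 58 | 1 |

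Differences are in percentage points, taken before rounding.

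**If Bonferroni spans the three moments** (0.05/3 = 0.0167), the level test has 31, 20, 10 and 5% power at r = 0.7, 0.8, 0.9 and 0.95.

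**If 0.58 is in level-SD units instead**, the level test has 69% at every r. The change test runs from 69% (r = 0.5) to over 99% (r = 0.9), and the baseline-adjusted test from 81% to over 99%.

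**Chance imbalance, no treatment effect** (simulation, r = 0.8 to 0.95). When the arms differ at baseline by more than 1 standard error, which happens in about 32% of trials, the level test rejects in 14 to 16%. Near 2 standard errors it rejects in roughly 23 to 37%. The baseline-adjusted test stays at about 5% (4 to 6%). Averaged over all trials, the level test keeps about 5%.

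**Disagreement.** With a true effect of 0.58 change-SD, the change test rejected and the level test did not in 42% (r = 0.8), 53% (0.9) and 60% (0.95) of simulated trials.

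**The case against.** The strongest reply is that the same sentence already plans the comparison of changes, which is the powered quantity. The level contrasts can then be read as the usual follow-up comparisons of a repeated-measures model. On that reading the cost of not adjusting for baseline is the last column of the table, 1 to 12 points, and it is smallest where the level test looks worst. This stands.

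Other parts also stand:

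- A reader might infer that the level tests address a different null from the powered one. The documents do not support this at 4 and 12 months. Randomisation makes the expected baseline difference zero, so the expected differences in level and in change are equal. Only M1 has a different null.
- A reader might call these tests unadjusted. The Discussion promises control for age, retirement years and gender, so they are unadjusted only for the outcome's baseline value. The promised terms may recover some precision, which cannot be quantified from the article.
- The size of the gap depends on r and on the standardiser, and the article states neither. The alpha-split figures also suppose a Bonferroni family that it does not define.

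It can also be said that a condensed article may leave its covariate list to an analysis plan. That would excuse silence on baseline adjustment taken alone. It does not cover what the article does state: between-arm comparisons at all three moments, baseline included, side by side with the change comparison and with no order between them.

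**Conclusion.** The point holds as a matter of precision and clarity. The M1 test is uninformative by design. The level tests at 4 and 12 months estimate the right effect inefficiently when r exceeds 0.5. The sentence does not say which contrast decides the trial.

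With 37 per arm, two-sided 5% and 0.58 in change-SD units, baseline adjustment gains 12 to 58 points of power over the level tests across r = 0.5 to 0.95, but only about 1 to 12 points over the planned change comparison. In level-SD units the level test has 69% and the adjusted test 81% or more.

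Two stronger readings fail. The trial does not fail to test its powered hypothesis, and it does not lose up to 58 points as a whole, because the change comparison is planned. Nor is the overall type I error of a single level test inflated; the excess rejections arise only in trials with a chance baseline difference. The change is worth making because it uses data already collected and costs almost nothing.

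**What to change.** In section 3.3.6:

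- Remove the between-arm test at M1 and the level tests at M2 and M3 that are not adjusted for baseline.
- State that the arms are compared on total and abdominal fat at 4 and 12 months with the participant's own baseline value as covariate. Use either an ANCOVA at each follow-up, or a repeated-measures model with the two follow-up values as outcomes and a baseline-by-time term.
- Keep the sex, age and retirement-years terms already promised.
- Say which of these comparisons decides the trial.
- Apply Bonferroni only to post-randomisation comparisons.
- Treat each secondary outcome that has a baseline value in the same way.

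The cost is one or two sentences of text and one or two degrees of freedom. It needs no new data, visits or participants, and the planned software can run it.

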## Abstract

Preventive and educational programs directed to former elite athletes in the areas of healthy living are required. This is particularly relevant as obesity and health-related problems are observed in retired athletes, especially in those whose current levels of physical activity are below the recommendations. During their sports career, elite athletes are supported by a multidisciplinary team; upon retirement, no support is provided for the transition to a different lifestyle. So far, no program has been implemented to promote sustained healthy lifestyle behaviors in the post-career transition and evidence is lacking for such an intervention. Firstly, we aim to determine if Champ4life, a 1-year lifestyle intervention targeting inactive former athletes with overweight and obesity, is effective for reducing total and abdominal fat. Secondly, our purpose is to assess the effectiveness of the intervention on the levels of physical activity and sedentary behavior, resting energy expenditure, cardio-metabolic markers, physical fitness, energy balance components, eating self-regulation markers, and quality of life over 12 months. Champ4life is an evidence- and theory-based program using a randomized control trial design (intervention vs. control group) that will be conducted on 94 inactive former elite athletes with overweight and obesity. The first four months of the Champ4Life program include a nutritional appointment and 12 weekly, 90-min sessions. Classroom sessions seek to provide participants with key information and a toolbox of behavior change techniques to initiate and sustain long-term lifestyle changes. Participants will undergo baseline, 4-month, and 12-month measurements of body composition (primary outcomes), resting energy expenditure, physical fitness, metabolic markers, energy balance related-markers, and quality of life (secondary outcome). This trial will provide evidence on the effectiveness of the Champ4life program, a pioneer lifestyle intervention for retired athletes, offering tools for sustained changes in physical activity, sedentary behavior and diet, aiming to improve body composition and overall health-related markers.

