In this regard, interventions that support autonomous motivation for physical activity may foster increased engagement in self-regulation techniques and positively affect lifestyle health behaviors [35]. A systematic review on effective behavior change interventions designed to promote PA and healthy eating [36] clearly supported the inclusion of multiple self-regulatory techniques, specifically self-monitoring of behavior in combination with prompt intention formation, prompting specific goal setting, providing feedback on performance, and prompting review of behavioral goals [37]. Therefore, the inclusion of self-regulatory skills within autonomy-supportive educational sessions brings added value to encourage the adoption of energy balance behaviors.

This paper describes the protocol for a randomized controlled trial, which aims to evaluate the effectiveness of the Champ4Life program in supporting former athletes to improve their lifestyles versus a waiting list control group that is offered the program after the 1-year follow-up. The primary aim of the trial is to determine whether Champ4Life can help inactive former athletes aged 18–65 years with a body mass index (BMI) ≥25 kg/m^2^ to reduce total and abdominal fat mass over 12 months. Secondary outcomes include cardio-metabolic blood biomarkers (e.g., glucose, insulin, HbA1c, lipids, liver function), adaptive thermogenesis blood-derived indices (leptin and thyroid function), weight and waist circumference, improvement in other body components (fat-free mass, water compartments), resting systolic and diastolic blood pressure, physical fitness (e.g., cardiorespiratory fitness, strength), free-living PA, sedentary time, energy balance regulation, eating self-regulation markers, and quality of life.

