#### 3.1.8. Energy Intake

When total energy expenditure (TEE) is obtained in conjunction with measured body composition, then two terms of the EB equation are known, namely EB and energy expenditure (EE). From the previous equation, we can estimate average energy intake during the course of the study. The magnitude of compensation will be calculated as the difference between achieved energy imbalance and EE. Three-day food records (with one-weekend day) will also be collected to characterize macronutrient composition of the diet in the three assessment sessions using a software package (Food Processor SQL, ESHA Research, Salem, OR, USA) by a registered dietitian. Comprehensive written instructions using specific guidelines, including pictures of portion sizes used for a better recording of food intake, and examples of common errors in recording dietary intake combined with face-to-face debriefing sessions will ensure accurate food records collection. At the end of the recording period, a registered dietitian will review the record with the participant to clarify potential omissions and ambiguities and to assure that additional information is provided to improve the accuracy of the macronutrient composition of the diet.

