### 3.3. Physical Fitness

#### 3.3.1. Cardiorespiratory Fitness Test

Maximal cardiorespiratory capacity will be assessed using the Bruce protocol test [71] performed on a variable speed and incline treadmill (Quinton Treadmill, Model 640, 90 TM Series). Simultaneously, the ventilated gas volumes, flow rates, and respiratory gas exchange will be determined by an open-circuit spirometry system (MedGraphics Corporation, Breezeex Software). Maximal oxygen uptake (VO_2_max) will be achieved when the two following criteria are obtained: a respiratory exchange ratio equal or greater than 1.10 for females and males aged to 20–49 y and equal or greater than 1.05 for females and males aged to 50–64 y [72], and no increase in VO_2_max despite further grade increases. The assessment will be performed at baseline and at 12 months.

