**Exclusion Criteria**
Failure to complete the run-in for dietary intake and physical activity; Unable/unwilling to give informed consent or communicate with local study staff; Inability to complete the study within the designated time frame because of plans to move out of the study area; Inability to attend the visits/appointments, evaluation measurements, and attend the intervention sessions at the FMH-UL; Schizophrenia, bipolar disorder, other psychotic disorders; Eating disorders; Major depression; Current consumption of more than 14 alcoholic drinks per week or other substance abuse, and/or current acute treatment or rehabilitation program for alcohol/substance abuse; Pregnancy/planning to get pregnant within the next 8 months; Having been pregnant within the past 6 months or breastfeeding; History of weight loss surgery or liposuction procedures; Current participation in a weight loss program; Losing >4.5 kg in the past three months; Current use of medications for weight loss; Thyroid disorders; Diabetes and cardiovascular disease; Other medical conditions known to affect energy balance homeostasis; Systemic corticosteroid treatment (weight gain associated with steroids may interfere with the intervention goals but use of hormone replacement therapy or oral contraceptives will not lead to exclusion).

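### Physical fitness is tested only at baseline and 12 months, so the 4-month measurement in the abstract and the three-moment analysis in Statistics cannot apply to it

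*Protocol article*

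**What the plan says.** The abstract states: "Participants will undergo baseline, 4-month, and 12-month measurements of body composition (primary outcomes), resting energy expenditure, physical fitness, metabolic markers". The same list goes on to energy balance markers and quality of life.

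The Introduction names fitness as a secondary outcome and says what is meant by it: "physical fitness (e.g., cardiorespiratory fitness, strength". Resting blood pressure is listed there as a separate item.

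Section 3.3.6 (Statistics) applies Bonferroni-corrected repeated measures to "differences between conditions at the three moments and for changes between the intervention and control groups over time in primary and secondary outcomes". No outcome is excepted.

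Section 3.3.1, on the cardiorespiratory test, says: "The assessment will be performed at baseline and at 12 months". Section 3.3.2 gives the same two times twice, once for handgrip and once for the leg press. Table 1 places the strength and cardiorespiratory tests in the third baseline visit (M1) and the second 12-month visit (M3). The single 4-month visit (M2) contains neither.

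On energy intake, section 3.1.8 solves the energy balance equation from body composition and total energy expenditure, and describes the result this way: "From the previous equation, we can estimate average energy intake during the course of the study". Three-day food records are collected at all three assessments, for the separate purpose of describing macronutrient composition.

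**The concern.** The article gives two incompatible accounts of when fitness is measured. The abstract and the analysis paragraph say three times; the measurement sections and the schedule say twice. Fitness is a named secondary outcome, and the Discussion expects it to improve, so the analysis that will support that claim should be one that can be run. As written, the analysis paragraph prescribes a three-moment comparison for data with two moments. It leaves open which contrast is the fitness result and which multiplicity correction goes with it.

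A smaller ambiguity concerns derived energy intake. An imbalance inferred from body composition needs two measurements, so the method yields a value for an interval and not for a moment. Read literally, the sentence on three moments for all secondary outcomes does not fit such a variable.

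**Working it through.** **Fitness: stated against scheduled moments**

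| Source | Baseline | 4 months | 12 months |
|---|---|---|---|
| Abstract (physical fitness) | yes | yes | yes |
| 3.3.6 Statistics (all secondary outcomes) | yes | yes | yes |
| 3.3.1 Cardiorespiratory test | yes | no | yes |
| 3.3.2 Handgrip | yes | no | yes |
| 3.3.2 Leg press | yes | no | yes |
| Table 1 (strength and cardiorespiratory tests) | yes | no | yes |

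Section 3.3 also holds blood pressure, exercise motivation and quality of life under its fitness heading. Table 1 has all three at the 4-month visit, so the conflict is confined to the tests in 3.3.1 and 3.3.2.

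**Contrasts available**

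With k moments there are k(k − 1)/2 pairwise time contrasts.
- Stated, k = 3: 3 × 2/2 = 3 contrasts. If the Bonferroni correction runs over these (the section does not say), each is tested at 0.05/3 = 0.0167.
- Scheduled, k = 2: 2 × 1/2 = 1 contrast (baseline to 12 months), tested at 0.05.

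**Precision of the two analyses that the schedule allows**

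With two moments, the group-by-time test is the between-arm comparison of change. Let σ² be the variance at each moment and ρ the correlation between baseline and 12 months.
- Variance of change: 2σ²(1 − ρ).
- Variance of the 12-month value after adjustment for baseline: σ²(1 − ρ²).
- Ratio, adjusted to change: (1 + ρ)/2.

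The document gives no ρ. As an assumed range:
- ρ = 0.5: (1 + 0.5)/2 = 0.75
- ρ = 0.7: (1 + 0.7)/2 = 0.85
- ρ = 0.9: (1 + 0.9)/2 = 0.95

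The adjusted analysis thus has 5% to 25% less variance over this range. The ratio is below 1 whenever ρ is below 1. The formulas ignore the one degree of freedom spent on the covariate.

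**Derived energy intake**

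Table 1 schedules DXA at M1, M2 and M3, with none before M1. Three measurements bound two intervals, M1–M2 (0 to 4 months) and M2–M3 (4 to 12 months). The method therefore gives at most two interval averages and no baseline value.

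**What is not affected**

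DXA is scheduled at all three moments, so the primary outcomes of total and abdominal fat can be analysed as planned. The sample size rests on total body fat and does not depend on this point.

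**The case against.** The strongest reply is that the operative text agrees with itself. Sections 3.3.1 and 3.3.2 and Table 1 all say baseline and 12 months, so staff would not be misled, and the fault is a loose list in an abstract. The Statistics sentence also covers changes between groups over time, and a group-by-time test is valid with two moments. This stands: correcting the abstract alone would be nearly clerical, and no valid fitness analysis is lost except the 4-month one. What remains is that the analysis section applies three moments to every secondary outcome. Once it is corrected, the baseline-adjusted comparison is the better use of the same data.

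On energy intake, the reply is that section 3.1.8 already calls the quantity an average over the study and that nothing promises a baseline value of it. The wider secondary-outcome list, "free-living PA, sedentary time, energy balance regulation, eating self-regulation markers, and quality of life", does not name derived intake. Reported diet is also recorded at all three assessments. This stands too, and it reduces the matter to a clarification.

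A reader might go further. Because recent weight loss is excluded only by "Losing >4.5 kg in the past three months", alongside current weight-loss programmes and medication, some participants could be losing weight at entry. Setting their baseline intake equal to expenditure would then distort the change in intake by about as much as the programme aims to achieve. The documents do not support this. They nowhere set baseline intake equal to expenditure. Loss at some time in the previous three months is not the same as loss at the baseline visit. A participant at the exclusion limit says nothing about a group mean. Under randomization such an error would add noise to individual changes, and no between-arm bias is expected from it.

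**Conclusion.** The inconsistency on fitness is confirmed. For cardiorespiratory fitness, handgrip and leg press, two of the three stated moments exist, so one contrast remains out of three and no 4-month comparison can be made. This follows from the text and the schedule and needs no assumption.

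The consequence is moderate. The 12-month fitness comparison is intact, and the primary outcomes and sample size are untouched. A reader might infer that the planned fitness analysis fails altogether; it does not, because the two-moment comparison is valid. The gain from baseline adjustment is real, but its size depends on a correlation that the document does not give. The 5% to 25% range assumes ρ between 0.5 and 0.9 and equal variance at the two times.

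The point on derived energy intake is an inference from the method in section 3.1.8 and is a minor clarification only.

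**What to change.** 1. Abstract: state that physical fitness is measured at baseline and 12 months.
2. Section 3.3.6: except cardiorespiratory fitness, handgrip and leg press from the three-moment analysis. Analyse each as the between-arm difference at 12 months, adjusted for its own baseline value, with no correction across time points because there is only one contrast.
3. Section 3.1.8 or 3.3.6: state that derived energy intake is an average over M1–M2 and over M2–M3, compared between arms within each interval and not reported as a change from baseline.

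The cost is wording. No visit, test or participant is added, and the adjusted model spends one degree of freedom on the covariate. What is given up is a 4-month fitness result and a change from baseline in derived intake, neither of which the schedule can supply.
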